#### Cognitive function

Montreal Cognitive Assessment (MoCA) is a brief 10-min, 30-item, one-page cognitive screening, diagnostic and tracking tool with high sensitivity and specificity for detecting MCI [43, 57]. It is widely used internationally and has been translated into many languages. It assesses several cognitive domains such as memory, executive function, attention, language, abstraction, naming, delayed recalls, and orientation.

#### Memory

The Memory Index Score of the Montreal Cognitive Assessment (MoCA-MIS) consists of 15 items on memory and validated to help determine in predicting conversion to Alzheimer’s disease or dementia from MCI over 18 months [58]. It is calculated by getting the sum of the number of words correctly remembered by the participant in free delayed recall, category cued recall, and multiple choice-cued recall multiplied by 3, 2 and 1, respectively, to obtain a score which ranges from 0 to 15 [58].

#### Executive function

Executive Function Performance Test (EFPT) is a valid and reliable instrument that uses structured cueing and scoring system to examine executive function in doing basic real-world tasks like hand-washing, oatmeal preparation, telephone use, taking medication, and paying bills [59]. To consider the local context, only the use of the telephone and taking of medication will be performed in this study.

#### Balance

The Timed Up and Go Test (TUGT) will be used to examine the dynamic balance of the participants. It is a simple and reliable [60] test that measures the time in seconds it takes a person to stand up from a chair, walk a distance of three meters, turn around, walk back towards the chair and sit down again. It is a sensitive and specific tool for identifying older adults who are at risk of falls [61]. Those who take longer than 14 s to complete this test have a high risk of falls [61].

#### Gait speed

Gait speed will be measured using the 10-Meter Walk Test (10MWT). This is a valid and reliable gait speed assessment in older adults [62]. It is the quotient of distance covered in meters, and the duration in seconds it takes the participant to walk that distance. The participants will perform the test at their preferred speed and fastest speed possible [62, 63].

#### Muscle strength

The strength of the lower limb muscles will be assessed using the 30s-Chair-Stand Test (CST). This is done by asking the participants to perform sit-to-stand on a standardized chair as many as they can within 30 s. The CST has excellent validity and reliability in community-dwelling older persons [64].

#### Fear of falling

The Falls Efficacy Scale – International (FES-I) will be used to assess the fear of falling of the participants. The tool is composed of 16 items. Each item is scored based on a four-point scale (1 = not at all concerned; 2 = somewhat concerned; 3 moderately concerned; and 4 = very concerned). The score ranges from 16 to 64. A high score means more fear of falling. FES-I has been shown to have excellent psychometric properties including construct validity, internal consistency, and test-retest reliability and discriminatory power when used in older persons [65–68].

#### Quality of life

Perceived Well-Being (PWB) Scale is a brief and easy to use tool that measures the quality of life specifically in the domains of psychological and physical well-being. It has high internal consistency and validity and is significantly correlated with variables that affect an individual’s well-being [69]. The score ranges from 16 to 116. A high score means greater perceived well-being.

#### Health status

EuroQoL-5 dimensions-5 levels (EQ-5D-5 L) is a valid and standardized tool developed to provide a simple, generic measure of health status for clinical and economic analysis [70]. The five dimensions are mobility, self-care, usual activities, pain/discomfort, and anxiety/depression. Each dimension has five levels: no problems, slight problems, moderate problems, severe problems, and extreme problems [71]. The tool has shown evidence of responsiveness to change [72]. It has been translated into over 120 languages and the validated Tagalog version of EQ-5D-5 L will be used with permission in this study.

### Statistical analysis

Descriptive statistics will be used to summarize demographic data using mean standard deviations, and percentages. Baseline values across the groups will be compared using one-way ANOVA for interval/ratio data and Kruskal-Wallis test for nominal/ordinal data. The multivariate repeated measure ANOVA will be used to determine the pre- and post-intervention effects and differences among group data with a normal distribution; otherwise the Friedman test will be utilized. The incidence rate ratio, computed as the number of falls divided by the duration of falls monitoring for every participant, will be used to compare intergroup fall rate. An intention-to-treat analysis will be used for missing data due to dropouts. The *p*-value of < 0.05 is considered significant. Data analysis will be performed using SPSS version 23 for Windows.

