### Study design and procedures

This proposed study is a randomized controlled trial using a 4-group design including three intervention groups (physical training alone or cognitive training alone, or combined physical and cognitive training) and one waitlist control group. The study will comply with the principles of the Declaration of Helsinki 2013 and Good Clinical Practice Guidelines. Ethics approval was secured from the Human Subjects Ethics Sub-committee of the Hong Kong Polytechnic University-Department of Rehabilitation Sciences (HSEARS20170402001) and the Ethics Review Committee of the University of Santo Tomas-College of Rehabilitation Sciences (FI-2017-002). The SPIRIT guidelines were followed in the design of this study protocol.

Trained study personnel will interview the participants using questionnaires to obtain their demographic information and medical history, physical activity level and history of falls, and will conduct cognitive and physical performance tests to determine their eligibility to participate in this study. Only those who signed the informed consent will be included in this study.

Random allocation will be carried out by a third party not involved in the study by random draw to blindly allocate each participant to one of the four groups. To minimize experimental contamination through social interaction and communication among the participants, the interventions will be delivered at different sites.

Measurement points include baseline/pre-intervention, post-intervention, and six months follow-up assessments and will be conducted by trained study personnel blinded to the randomization assignment. Physiotherapists and occupational therapists who will be administering the interventions will not be involved in the outcome assessment. They will also have workshops and discussions to standardize the administration of the different training programs. After the intervention period, aside from a calendar-diary, monthly phone calls will also be done to follow up the participants about their fall status, physical activity, and exercise behavior. Figure 1 illustrates the study flow. Appendix shows the timeline of the study.

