### Sample size computation

The sample size and power calculations will be based on fall rate which is the primary outcome of the study. Using statistical software Gpower 3.1.9.2, a priori power analysis was conducted using the computed effect size (Cohen’s d = .39) from Trombetti et al. (2011) [46]. Assuming 80% power with 5% Type 1 error and four groups, the calculated total sample size is 80. Considering a 16% dropout rate (Trombetti et al., 2011) [46], the total number of participants is inflated to 93. There should be at least 23 participants per group.

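### The Kruskal-Wallis test is assigned to nominal baseline data, so for an unordered variable with three or more categories the p-value depends on arbitrary code numbers: a minor correction confined to the baseline comparison

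*Protocol article*

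**What the plan says.** The Statistical analysis section sorts baseline variables into two classes and gives each a test: "Baseline values across the groups will be compared using one-way ANOVA for interval/ratio data and Kruskal-Wallis test for nominal/ordinal data". The threshold is that a p-value "value of < 0.05 is considered significant". No chi-square, Fisher or other test for unordered categories appears anywhere in the article.

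The plan does expect categorical baseline data. Under Study design and procedures, interviews will "obtain their demographic information and medical history, physical activity level and history of falls". The Statistical analysis section adds: "Descriptive statistics will be used to summarize demographic data using mean standard deviations, and percentages". Individual demographic and medical-history variables, and their numbers of categories, are not listed.

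The comparison is across the arms of a "randomized controlled trial using a 4-group design", and Sample size computation says: "There should be at least 23 participants per group".

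**The concern.** Kruskal-Wallis asks whether values in some arms tend to rank higher than in others. That is a sensible question for ordinal data. It has no meaning for a nominal variable, because the order of the categories is whatever order the code numbers happen to have. With three or more categories, two analysts holding the same participants and equally valid codes can obtain different p-values.

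The direction of the error matters too. If arms differ mainly in the category that happens to carry the middle code, the mean ranks can coincide and the test sees nothing.

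At stake is the credibility of the baseline table in a trial with about 23 participants per arm, where chance imbalances can be sizeable. A p-value near 1 beside visibly different percentages would mislead a reader. This is a rule that the article states, not a detail left for a fuller document.

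**Working it through.** The article gives no figure on this point, so there is nothing to reproduce. The check compares the stated test with chi-square on illustrative tables.

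**Inputs from the article:** four arms (Study design and procedures); 23 per arm, so N = 92 (Sample size computation; the article's total is 93); threshold 0.05 (Statistical analysis).

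**Assumption:** one nominal variable with categories A, B, C and the counts below.

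| Arm | A | B | C |
|---|---|---|---|
| 1 | 10 | 3 | 10 |
| 2 | 3 | 17 | 3 |
| 3 | 8 | 7 | 8 |
| 4 | 8 | 7 | 8 |
| Total | 29 | 34 | 29 |

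Category B holds 3/23 = 13% of arm 1, 17/23 = 74% of arm 2, and 7/23 = 30% of arms 3 and 4.

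**Step 1, chi-square.** X² = Σ(O − E)²/E. Each arm's expected counts are 29/4 = 7.25, 34/4 = 8.5 and 7.25. The contributions are 5.65 (arm 1), 13.48 (arm 2) and 0.42 each (arms 3 and 4). The sum is 19.97 on 6 df, p = 0.0028. No recoding changes this.

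**Step 2, Kruskal-Wallis with A=1, B=2, C=3.** H = [12/(N(N+1))] Σ nᵢ(R̄ᵢ − (N+1)/2)² / T, where T = 1 − Σ(t³ − t)/(N³ − N) corrects for ties.
- Midranks: A 15, B 46.5, C 78.
- Every arm has equal numbers in A and C, so every mean rank is 46.5 = (N+1)/2.
- H = 0, p = 1.00.

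**Step 3, the same participants with A=1, B=3, C=2.**
- Midranks: A 15, C 44, B 75.5.
- Mean ranks: 35.5, 63.5, 43.5, 43.5. Deviations from 46.5: −11, 17, −3, −3.
- Sum of squares: 121 + 289 + 9 + 9 = 428.
- Uncorrected H = 12/(92 × 93) × 23 × 428 = 13.81; T = 0.887; H = 15.57 on 3 df, p = 0.0014.

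Relabelling two categories therefore moves the p-value from 1.00 to 0.001.

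**Step 4, two further illustrative tables.**

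| Counts by arm | Chi-square p | Kruskal-Wallis p, codes 1,2,3 | codes 1,3,2 | codes 2,1,3 |
|---|---|---|---|---|
| 10/3/10, 5/13/5, 9/5/9, 6/11/6 | 0.043 | 1.00 | 0.020 | 0.020 |
| 12/6/5, 9/7/7, 5/7/11, 4/7/12 | 0.156 | 0.031 | 0.301 | 0.584 |

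The other three codings are reversals of these and give the same p-values.

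**Step 5, limits of the problem.**
- *Two categories.* H = X² × (N − 1)/N. For counts 18/5, 14/9, 19/4, 11/12: X² = 8.112, and 8.112 × 91/92 = 8.024; p = 0.044 against 0.046. Coding is immaterial.
- *Type I error.* With identical category shares in all arms (0.40, 0.35, 0.25; 20,000 simulated trials), any one fixed coding rejects in 4.7 to 4.8% of trials and chi-square in 4.7%. At least one of the three distinct codings rejects in 11.9%, but that needs someone to try them all.

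**The case against.** The strongest reply is that no affected variable is shown. The nominal features the article does name are binary: sex, use or not of an assistive device, low or high fall risk. The EQ-5D-5L levels are ordered, so Kruskal-Wallis suits them. This stands as a limit on reach. It does not rescue the rule, which names nominal data without restriction and would govern any multi-category demographic or medical-history item.

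Second, nothing in the plan hangs on the result. No covariate choice, adjustment or primary analysis is tied to a baseline p-value, and the planned percentages would themselves expose an imbalance like the one above. That also stands, and it keeps the point small.

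Third, the main worked table is symmetric about the middle code, which is the worst case for a rank test. True: it shows what can happen, not how often.

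Some stronger readings are tempting and should be resisted:
- A reader might infer that the test systematically invents imbalances. It does not, because a coding fixed in advance keeps its error rate near 5%. Under Data monitoring, the data are also encoded by one person blinded to allocation, so there is no ground to suspect codes chosen with knowledge of the arms.
- A reader might want to quote the test's power against a true baseline difference between arms. Under sound randomisation there is no such difference to detect, so a power figure would not describe this trial.
- A reader might object to all baseline significance testing, or compute the chance of some p < 0.05 over many tests. That is a separate reporting preference. The calculation would need a count of independent tests that the article does not give, and several of its measures are related (the MoCA memory index derives from the MoCA).

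**Conclusion.** The concern holds as a minor correction. The article assigns a rank test to nominal data. For an unordered variable with three or more categories that makes the p-value a product of arbitrary codes, and it can hide a visible imbalance: chi-square p = 0.003 against Kruskal-Wallis p = 1.00 or 0.001 in the worked table.

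This rests on two assumptions: that at least one such variable is among the baseline items tested, and that the illustrative counts are within the range of what arms of 23 could show. A reader might infer that the falls comparison or the trial's conclusions are compromised. The article does not support that, since the effect stops at the baseline comparison.

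**What to change.** In the Statistical analysis section, replace the nominal/ordinal clause so that nominal baseline variables are compared by chi-square, or by the Fisher-Freeman-Halton exact test where expected counts are small, and Kruskal-Wallis is kept for ordinal variables only. Chi-square on the three tables above gives a single p-value each (0.003, 0.043 and 0.156) whatever the codes.

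Optionally, present the baseline table descriptively without p-values, which removes the question altogether. The drawback is that readers who expect a p-value column will not find one.

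Either change is one line of wording. It needs no new data, staff or participants.

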On the contrary, a study that combined resistance training and cognitive training in older adults with MCI concluded that doing high-intensity resistive training alone for six months lead to significant increase in global cognitive function, memory and executive function while participating in combined training unexpectedly and significantly reduced the benefits of isolated progressive resistance training on executive and global cognitive function [39]. In another study also involving older persons with MCI, dual modality cognitive-physical training and single modality interventions of cognitive training alone or physical exercise alone resulted in no significant differences in cognitive outcome measures [40]. In a systematic review, both older adults with and without cognitive impairment gained improvements in cognitive functions and functional status from combined physical exercise and cognitive training interventions [41]. However, the evidence is lacking to ascertain the superiority of combined interventions when compared to active control groups. More studies with good methodological quality are warranted to explore the potential benefits of this new treatment approach [41].

The link connecting the improvements in cognitive function and physical factors after undergoing physical exercise and cognitive training, singly delivered or in combination, to the reduction of falls and the decrease in falls risk in the geriatric population, particularly to those with MCI, is yet to be established.

Thus, this study primarily aims to determine the effectiveness of combined physical and cognitive training on preventing falls and reducing the risk of falls among community-dwelling older adults with MCI. The hypothesis is that an intervention that incorporates elements of both physical exercise and cognitive training in one treatment program is more effective compared to physical exercise or cognitive training alone in preventing the occurrence of falls and in decreasing the risk of falls in older adults with MCI living in the community.

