## Methods

### Participants

Community-dwelling older adults, both male and female, aged 60 or above with MCI will be included. They will be recruited from community sites in Manila, Philippines through the assistance of local coordinators of the Office of Senior Citizens Affairs (OSCA) of Manila. The presence of MCI will be established following the criteria of Winblad et al. (2004) [42]. A person is diagnosed to have MCI if 1) the cognitive function is not normal nor demented; 2) there is subjective report of the individual and/or informant on declining cognitive function compared to five years ago [5] on objective cognitive tasks; and 3) the performance of basic ADLs is preserved with only minor problems doing complex instrumental ADLs [42]. Not normal cognitive function or presence of mild impairment will be based on Montreal Cognitive Assessment (MoCA) score of < 26 [43]. Not demented will be based on not having a medical diagnosis of dementia or Alzheimer’s disease [5, 44]. Normal function in ADL and no or minimal impairment in instrumental ADL will be based on Katz ADL Scale [45] and Lawton Instrumental Activities of Daily Living (IADL) Scale [4]. A trained neurologist-psychiatrist will examine the participants to provide the final diagnosis of MCI and give them the clearance to participate in the exercise. Only ambulatory older adults, with or without an assistive device, will be included since the interventions are community-based.

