### Outcomes measures

The following primary and secondary outcome measures will be performed by trained assessors blinded to the group allocation. Measurements will be taken at baseline, at the conclusion of the intervention period, and 6 months post-intervention. Additional information regarding the exercise behavior and the physical and social activities participated in by the eligible participants in the last 6 months will be obtained during the 6 months post-intervention follow-up assessments [52].

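### The repeated-measures ANOVA for normally distributed secondary outcomes treats baseline as an outcome and does not identify the between-arm contrast that answers the hypothesis

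*Protocol article*

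**What the plan says.** The Statistical analysis section of the Protocol article gives one sentence to the continuous outcomes: "The multivariate repeated measure ANOVA will be used to determine the pre- and post-intervention effects and differences among group data with a normal distribution". For non-normal data it adds "otherwise the Friedman test will be utilized"; that fallback is not the subject here. Baseline appears once more, in a comparison of arms before treatment: "Baseline values across the groups will be compared using one-way ANOVA for interval/ratio data and Kruskal-Wallis test for nominal/ordinal data". No adjustment for baseline in the outcome analysis is mentioned. The significance threshold is a p-"value of < 0.05 is considered significant".

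The design has four randomised arms (Study design and procedures). On timing, the Outcomes measures section says: "Measurements will be taken at baseline, at the conclusion of the intervention period, and 6 months post-intervention". The hypothesis, at the end of the Background, is comparative: the combined programme "is more effective compared to physical exercise or cognitive training alone in preventing the occurrence of falls and in decreasing the risk of falls". Fall rate has its own rate comparison in the same Statistical analysis section and lies outside this sentence.

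**The concern.** The treatment question is whether arms differ after training. A repeated-measures ANOVA over baseline and follow-up yields three tests with three different nulls: change over time pooled over arms, arm means pooled over visits, and arm differences in change. The wording comes closest to the first two, and the third, which carries the treatment question, is not picked out.

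This matters in two ways. First, change shared by all arms is plausible: the same performance tests are repeated at each visit, and MoCA is both an outcome and an entry criterion ("presence of mild impairment will be based on Montreal Cognitive Assessment (MoCA) score of < 26"), so some regression to the mean is expected in every arm. A pooled time effect would pick this up and says nothing about the arms. Second, a model that spends the baseline measurement as an outcome generally uses it less efficiently than one that adjusts for it. The aim of reducing the risk of falls rests on these secondary outcomes, and 20 evaluable participants per arm leave little precision to give away.

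**Working it through.** The article gives no figure for this analysis, so there is none to reproduce.

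**Inputs from the Protocol article:** 4 arms; 80 evaluable participants (Sample size computation), so n = 20 per arm; significance level 0.05; three visits, although the ANOVA sentence speaks only of pre and post.

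**Assumptions (not in the article):** outcome SD 1; equal correlation ρ between visits, 0.3 to 0.8; an effect D = 0.8 SD in one arm with the other three equal; a shared change of 0.4 SD for the time effect.

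**Step 1. Time effect.** With no arm difference and a shared change δ = 0.4 in all 80 participants, the noncentrality is 80 × δ² × ½ / (1 − ρ) = 6.4/(1 − ρ) for two visits, and 80 × δ² × ⅔ / (1 − ρ) = 8.53/(1 − ρ) for three. Simulation (4,000 trials per setting) finds it significant in 84–100% of trials with two visits and 89–100% with three, for ρ from 0.3 to 0.8. The test correctly detects a real change; it does not compare arms.

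**Step 2. Group main effect.** It compares arm means averaged over visits, and randomisation makes the expected baseline difference zero. The arm difference becomes:

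- two visits: (0 + D)/2 = D/2, so 0.8 becomes 0.40
- three visits, sustained effect: (0 + D + D)/3 = 2D/3, so 0.8 becomes 0.53
- three visits, effect at post only: (0 + D + 0)/3 = D/3, so 0.8 becomes 0.27

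This is algebra and needs no assumed correlation. Simulated type I error was 4.7–5.8%.

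**Step 3. Power for the arm question.** With one arm at D and three at 0, the sum of squared deviations of the arm means is D² × ¾ = 0.64 × 0.75 = 0.48, and n times this is 9.6. The noncentralities are:

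- group main effect, two visits: 9.6 × ¼ / [(1 + ρ)/2]
- group main effect, three visits, sustained: 9.6 × 4/9 / [(1 + 2ρ)/3]
- interaction, two visits (change score): 9.6 / [2(1 − ρ)]
- interaction, three visits, sustained (univariate F): 9.6 × ⅔ / (1 − ρ)
- ANCOVA at post: 9.6 / (1 − ρ²)
- ANCOVA on the mean of both follow-ups: 9.6 / [(1 + ρ)/2 − ρ²]

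At ρ = 0.5, for example, the two-visit change score gives 9.6/1.00 = 9.6 and ANCOVA at post gives 9.6/0.75 = 12.8. Power (%) from the noncentral F distribution:

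| ρ | Group, 2 visits | Group, 3 visits | Interaction, 2 visits | Interaction, 3 visits | ANCOVA, post | ANCOVA, mean of follow-ups |
|---|---|---|---|---|---|---|
| 0.3 | 31.7 | 62.9 | 55.6 | 57.7 | 76.2 | 93.8 |
| 0.5 | 27.8 | 52.4 | 71.8 | 75.0 | 84.5 | 96.1 |
| 0.6 | 26.2 | 48.2 | 81.9 | 85.3 | 90.1 | 97.9 |
| 0.7 | 24.8 | 44.6 | 92.1 | 94.6 | 95.8 | 99.4 |
| 0.8 | 23.6 | 41.4 | 98.8 | 99.5 | 99.4 | 100.0 |

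The ANCOVA columns ignore the small loss from chance baseline imbalance. Simulation of the group, interaction and ANCOVA-at-post tests at ρ = 0.3, 0.5, 0.7 and 0.8 agrees within about 1.5 points. Over all simulated forms of the interaction, including the multivariate test, its power was 70–75% at ρ = 0.5 and 81–86% at 0.6. Its type I error was 4–6% when all arms changed equally.

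**Step 4. Why adjustment gains.** The ratio of change-score to ANCOVA variance is 2(1 − ρ)/(1 − ρ²) = 2/(1 + ρ): 1.33 at ρ = 0.5 and 1.11 at ρ = 0.8. The gain is therefore largest when visits are weakly correlated.

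**The case against.** The strongest reply is that the sentence is loose, not wrong. A repeated-measures ANOVA with four groups contains the group-by-time term by construction, and the wording can be taken to mean arm differences in pre-post change. The stated aims are comparative and there is a waitlist arm, so shared practice effects and regression to the mean cancel in expectation in any arm contrast. Which model term decides is often left to an analysis plan, and none is shown here.

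Much of this stands. A reader might infer that only the two main effects will be examined, that a pooled time effect will be claimed as benefit, or that the trial's type I error is inflated. The article says none of these things. The within-person fallback for non-normal data leans towards a focus on change over time, but it does not settle the matter. Nor is the group main effect always the weakest choice: at ρ = 0.3 with a sustained effect it slightly beats the interaction (63% against 58%), and it trails ANCOVA at post by about 13 points. Losses of 30 points or more against ANCOVA at post belong to the literal group-effect reading at assumed correlations of 0.5–0.8.

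The reply does not remove the point. The article does more than leave a detail open: it fixes a model in which baseline is an outcome, and states a purpose that does not identify the arm contrast. Even on the kindest reading, a valid analysis of the same data is generally more powerful.

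**Conclusion.** The point holds as a weakness in a stated analysis choice, not as a validity failure. The planned model places baseline among the outcomes, and its stated purpose does not identify the contrast that the hypothesis needs.

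The size depends on which term is read. For the group main effect, dilution to one half or two thirds is certain given the visits and a sustained effect. For the interaction, the loss against ANCOVA at post is roughly 10–14 points at a correlation of 0.5 and 4–9 points at 0.6, and it largely closes at 0.7–0.8. Averaging both follow-ups with baseline adjustment gives 96% or more from 0.5 upwards if the effect is sustained. These power figures rest on an assumed 0.8 SD effect in one arm, equal correlation between visits and 20 complete participants per arm; the article gives none of the effect or correlation values for these outcomes.

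The reach is limited to secondary outcomes that prove normally distributed. Fall rate is untouched. The stronger inference, that the plan tests the wrong nulls and will report shared change as efficacy, goes beyond the text.

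**What to change.** Replace the ANOVA sentence with wording such as: For each continuous secondary outcome, arms will be compared at post-intervention and at 6 months by ANCOVA, or by a mixed model with arm-by-visit terms, with the baseline value as covariate. Adjusted differences of PACT versus PT, CT and WG will be reported with 95% confidence intervals. Changes from baseline within arms, or pooled over arms, are descriptive and will not be used to claim effectiveness.

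The cost is a few lines of text. Baseline values are already collected, the named software fits both models, and no further participants or visits are needed. The only thing given up is the use of pre/post p-values as evidence of benefit.

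### For non-normal secondary outcomes the named fallback, the Friedman test, cannot compare the four randomised arms

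*Protocol article*

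**What the plan says.** The Statistical analysis section of the protocol article gives one method two tasks. "The multivariate repeated measure ANOVA will be used to determine the pre- and post-intervention effects", and the sentence goes on to cover "differences among group data with a normal distribution; otherwise the Friedman test will be utilized". No other non-parametric test is named for follow-up data. Kruskal-Wallis appears once, for baseline only: "Baseline values across the groups will be compared using one-way ANOVA for interval/ratio data and Kruskal-Wallis test for nominal/ordinal data".

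Falls rate, the single primary outcome, has a separate sentence. It is to be compared between groups by an incidence rate ratio built from each participant's falls over monitored time.

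Under Study design and procedures the trial is a "randomized controlled trial using a 4-group design including three intervention groups" plus a waitlist control. Allocation is "by random draw to blindly allocate each participant to one of the four groups", and "Measurement points include baseline/pre-intervention, post-intervention, and six months follow-up assessments" are listed. The hypothesis, at the end of the Background, is that the combined programme "is more effective compared to physical exercise or cognitive training alone in preventing the occurrence of falls" and in lowering fall risk.

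**The concern.** The ANOVA has a between-subjects factor (arm) and a within-subjects factor (visit), so it can address group differences. Its stated replacement has only the within-subjects part. Any outcome that fails the normality condition therefore moves from a test that can address the trial's question to one that cannot.

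The secondary outcomes that serve the fall-risk half of the objective are the ones exposed. FROP-Com is a three-item score from 0 to 9, FES-I a sum of four-point items from 16 to 64, EQ-5D-5L a set of five-level dimensions, and the Timed Up and Go a time in seconds. Non-normality is plausible for several of these, although the protocol gives no distributional data. For any outcome sent to the fallback, the plan would have no valid test of PACT against PT, CT or WG.

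**Working it through.** There is no stated figure to reproduce. The check is of what the named test can and cannot detect.

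**Inputs from the protocol article.** Four arms; each person in one arm only; three measurement times (Study design and procedures); 80 analysable participants before dropout inflation, hence 80/4 = 20 per arm (Sample size computation); significance at p < 0.05 (Statistical analysis).

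**Step 1: the ways Friedman could be applied here.**

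1. *Visits as the conditions, all arms pooled.* Each person's three values are ranked 1 to 3 and the rank sums are compared across visits. The arm label does not enter the statistic. As a check, reordering 80 simulated participants left it unchanged (chi-square 4.975, p = 0.083 both times).
2. *Arms as the conditions.* This needs blocks in which each arm contributes one matched observation. Individual random draw creates no such blocks. It also needs equal arm sizes, and the planned 93 participants cannot split equally (93/4 = 23.25).
3. *Visits as the conditions, separately in each arm.* This gives four within-arm p-values and no between-arm test.

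None of the three tests a difference among arms.

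**Step 2: simulation of use 1 against a rank test that does compare arms.** Assumptions, none of them from the protocol: lognormal outcome; standard deviation 0.7 between and 0.7 within participants on the log scale; a common shift of 0.5, or arm shifts of -0.75, -0.25, 0.25 and 0.75, at both follow-up visits; 4,000 runs. The comparison test is Kruskal-Wallis across arms on change from baseline to the first follow-up.

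| Setting | Friedman rejects | Kruskal-Wallis on change rejects |
|---|---|---|
| No change, no arm difference | 5.3% | 4.7% |
| All arms change equally | 98% | 4.5% |
| Arms differ, average shift zero | 3.5% | 96% |

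Friedman responds to change over time that all arms share. It does not respond to arm differences that cancel on average.

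**Step 3: use 3, if its results were contrasted.** Suppose all arms change equally and each arm's Friedman test rejects with probability p. The arms are independent, so

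P(PACT significant, WG not) = p(1 - p).

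- p = 0.05 (no change in any arm): 0.05 x 0.95 = 0.0475
- p = 0.2 or 0.8: 0.2 x 0.8 = 0.16
- p = 0.5: 0.5 x 0.5 = 0.25, the maximum, since the slope 1 - 2p is zero there

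The protocol gives no value for p, so only the range is informative.

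**The case against.** The strongest case on the other side is about scope.

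- *A reader might infer that every skewed outcome, fall counts included, loses its between-group test.* The text does not support that. Falls rate has its own incidence rate ratio sentence and does not depend on the Friedman branch. Any weakness in that sentence is a separate matter.
- *The branch is conditional.* It applies only to outcomes judged non-normal, and no data on distributions are given. That stands: the number of outcomes affected is unknown.
- *A reader might take the 25% as the plan's false-positive rate.* It is not. The protocol does not propose to contrast within-arm p-values, and 25% is the peak of a curve over an assumed power. It shows the cost of a misuse that the fallback invites.
- *A reader might add that Friedman needs complete data at all visits.* Classical multivariate repeated-measures ANOVA has the same limit, so this does not count against the fallback in particular.
- *A fuller analysis plan may settle it.* The article names a test that cannot do the task. A fuller plan would have to contradict that sentence, not just add detail.
- *Friedman may be meant only for the pre/post effects.* Then non-normal outcomes have no between-arm test at all, since Kruskal-Wallis is confined to baseline. The gap is the same.

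**Conclusion.** Wrong as written, within a limited scope. For secondary outcomes judged non-normal, the stated fallback cannot test differences among the four individually randomised arms, so it cannot address the trial's hypothesis for those outcomes. This follows from the definition of the test and the allocation described; it does not depend on the simulation. The simulated rates (98% and 3.5%) depend on the assumed effects and variances. The p(1 - p) range of about 5% to 25%, for p from 0.05 up to the peak at 0.5, depends on an assumed per-arm power and on a contrast that the protocol does not propose. The primary falls-rate comparison is not affected.

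There is one minor related point. The baseline sentence assigns "Kruskal-Wallis test for nominal/ordinal data". For an unordered variable with more than two categories, the result depends on how the categories are coded. This touches baseline description only and no treatment-effect conclusion.

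**What to change.** Replace Friedman in the Statistical analysis section with a fallback that compares independent arms. Either of these would do:

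- a generalized linear mixed model or GEE with arm, visit, arm-by-visit and baseline value, using a distribution suited to the outcome; or
- Kruskal-Wallis across the four arms on change from baseline at each follow-up, with Mann-Whitney tests for PACT vs PT, PACT vs CT and PACT vs WG.

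Which one is chosen is a matter of preference; that it has an arm comparison is not. State also that efficacy will not be inferred from within-arm p-values. For unordered nominal baseline variables with more than two categories, use chi-square or Fisher's exact test, or description only.

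The cost is analysis wording. No visit, measurement or participant is added. The wording should be settled before outcome data are examined by arm, so that the replacement is not chosen with results in view.
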